## **6.3 Measures to Minimise Bias**

### **6.3.1 Part 1**

Part 1 is a sequential open-label study; potential bias will be reduced by the review of data by an IDMC.

### **6.3.2 Part 2**

#### **6.3.2.1 Randomisation and Blinding**

Part 2 is a randomised double-blind study.

All subjects will be randomised centrally using an interactive response technology (IRT) to ensure that treatment assignment is unbiased and concealed from study subjects and the Investigator. The Investigator will be provided with usernames and passwords for randomisation purposes and to unblind the study treatment in case of emergency, where he/she considers it essential to know what treatment the subject was taking. The IRT will be designed to send a confirmation (by fax and/or notification email) to the site for every transaction performed by the Investigator.

Each subject will be assigned to one of the 2 arms of the study according to the randomisation schedule provided by the Parexel Informatic Manager utilising a validated computer program. Details of the procedure are described in the IRT Manual provided to all sites.

Subjects will be randomly assigned in a 2:1 ratio to receive study treatment (XVR011 or placebo). Stratification will be done at randomisation for country and for fully vaccinated/prior SARS-CoV-2 infection. Any EMA approved, FDA approved or WHO recommended vaccine will be taken into account. The original recommended vaccination frequency (either 1 or 2 injections depending on the vaccine) will be considered as fully vaccinated, i.e. the more recent recommendations for a booster shot are not required for the stratification definition.

The placebo IV bag will present the same external appearance with the same composition, except for the active ingredient. IV bag cover will be added to keep the blinding on the IV bag.

Randomisation data will be kept strictly confidential, accessible only to authorised persons, until the time of unblinding of the allocated treatment of all study subjects after locking the database upon termination of the study.

Subjects, Investigators and/or employees of the investigational site will remain blinded to each subject's assigned study treatment throughout the course of the study, unless in case of emergency.

In order to maintain this blind, an otherwise uninvolved third party (unblinded pharmacist) will be responsible for the reconstitution and dispensation of all study treatment and will endeavour to ensure that there are no differences in time taken to dispense following randomisation.

The Sponsor will also be blinded during the study as they will not have direct access to the randomisation list or to the medication list. Specific sponsor representatives, independent of the study team will be unblinded to perform specific unblinded tasks.

In the event of a quality assurance audit, the auditor(s) will be allowed access to unblinded study treatment records at the site(s) to verify that randomisation/dispensing has been done accurately.

### **6.3.2.2 Procedures for breaking the blind**

In case of emergency, unblinding of the treatment code will be done through IRT (IWRS). The treatment group will be disclosed, and confirmation will follow (by fax and/or notification email). The IRT will promptly notify the Sponsor whenever a treatment code is unblinded.

An emergency medical contact service will be also available for part 2. The emergency phone number will be available on the subject ID card for the subjects enrolled in Part 2. This out-of-business-hours service allows the non-investigator healthcare professionals to access information on a 24-hour basis about study treatment being received by their subjects and providing the subject's study treatment allocation (i.e. unblinding).

## **6.4 Study Treatment Compliance**

Subjects are dosed at the site and will receive study treatment directly from the Investigator or designee, under medical supervision. The date and time of infusion, IV volume, infusion rate, and any infusion interruptions and restart will be recorded in the source documents and recorded in the CRF. The dose of study treatment and study subject identification will be confirmed at the time of dosing by a member of the study site staff other than the person administering the study treatment.

## **6.5 Concomitant Therapy**

Any medication or vaccine (including over-the-counter or prescription medicines, vitamins, and/or herbal supplements) that the subject is receiving at the time of enrolment or receives during the study must be recorded along with:

- reason for use
- dates of administration including start and end dates
- dosage information including dose and frequency

The Medical Monitor should be contacted if there are any questions regarding concomitant or prior therapy.

### 6.5.1 Standard of Care for COVID-19

Study treatments (XVR011 or placebo) should be administered in addition to SoC treatment per local institutional standards at the study site.

Owing to the extensive global effort to investigate and develop pharmacological and biological treatments of COVID-19 (including antiviral, immune-based, and adjunctive therapies), treatment recommendations are frequently updated and may vary across regions. The following treatment options are currently recommended by several regulatory authorities and/or expert panels:

- **Dexamethasone:** On 2 September 2020, based on a systematic review and meta-analysis of the results of 8 randomised controlled trials, WHO published a strong recommendation for the use of systemic corticosteroids in severely ill patients with COVID-19 and a conditional recommendation not to use systemic corticosteroids in patients with non-severe COVID-19 (WHO/2019-nCoV/Corticosteroids/2020.1, WHO REACT Working Group et al 2020). On 25 September 2020, the Infectious Diseases Society of America (IDSA) guideline panel also suggested dexamethasone for patients with severe COVID-19 ( $\text{SpO}_2 \leq 94\%$  on room air, including patients on supplemental oxygen). If dexamethasone is not available, then alternative glucocorticoids may be used. The IDSA guideline panel advises against glucocorticoids for patients with COVID-19 without hypoxemia requiring supplemental oxygen (Bhimraj et al 2020).
- **Remdesivir:** In May 2020, the FDA issued an emergency use authorisation (EUA) for remdesivir for the treatment of suspected or laboratory-confirmed COVID-19 in adults and children hospitalised with severe disease (FDA News Release 2020a). In June 2020, the FDA had warned against the use of remdesivir in combination with hydroxychloroquine (FDA News Release 2020b). In July 2020, the European Commission granted conditional marketing authorisation for remdesivir for the treatment of COVID-19 in adults and adolescents from 12 years of age with pneumonia who require supplemental oxygen (European Commission 2020), following recommendation from the EMA (EMA 2020), making remdesivir the first authorised COVID-19 antiviral treatment in the EU. In October 2020, the FDA approved remdesivir for use in adult and paediatric patients 12 years of age and older and weighing at least 40 kg (about 88 pounds) for the treatment of COVID-19 requiring hospitalisation (FDA News Release 2020c). In November 2020, the WHO issued a conditional recommendation against the use of remdesivir in hospitalised patients, regardless of disease severity, as there is

currently no evidence that remdesivir improves survival and other outcomes in these patients (WHO Living Guideline: Therapeutics and COVID-19, 20 November 2020).

See Table 6–4 for restricted concomitant medications and Table 6–5 for forbidden concomitant medications.

**Table 6–4 Restricted concomitant medications Part 1 only**

| Medication                                                                                            | Restriction                                                                               |
|-------------------------------------------------------------------------------------------------------|-------------------------------------------------------------------------------------------|
| Drugs showing possible anti-SARS-CoV-2 (antiviral) activity (including but not limited to remdesivir) | Within 30 days prior to study treatment administration and during the study up to the EOS |

COVID-19 = coronavirus disease 2019; EOS = end of study; SARS-CoV-2 = severe acute respiratory syndrome coronavirus 2

**Table 6–5 Forbidden concomitant medications**

| Medication                                                                                                                                            | Restriction                                                                               |
|-------------------------------------------------------------------------------------------------------------------------------------------------------|-------------------------------------------------------------------------------------------|
| SARS-CoV-2 hIVIG                                                                                                                                      | Within 30 days prior to study treatment administration and during the study up to the EOS |
| Convalescent plasma (convalescent plasma therapy) from a person who recovered from SARS-CoV-2 infection                                               |                                                                                           |
| Investigational or authorised biological medical product with a SARS-CoV-2 neutralising activity including but not limited to any monoclonal antibody |                                                                                           |
| Small molecule anti-SARS-CoV-2 medical product                                                                                                        | From signature of ICF up to EOS                                                           |

EOS = end of study; hIVIG = human intravenous immunoglobulin, mAb = monoclonal antibody, SARS-CoV-2 = severe acute respiratory syndrome coronavirus 2

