The IDMC will be asked to make a recommendation to progress to Part 2 (phase 2 design) of this study with the recommended dose based on the interim analysis of the Phase 1a study in 30 healthy subjects, supplemented with the available data from Part 1 of this study, even if not all Part 1 cohorts have reached the planned enrolment. This is due to recruitment challenges in Part 1 of this study resulting from low hospitalisation rate and reluctance of sites to participate and enrol patients in a phase I trial.

**Part 2 (Phase 2):** Part 2 consists of a double-blind, randomised, placebo-controlled Phase 2 study to evaluate the efficacy, safety, PK, and PD of XVR011 administered at the recommended dose level based on the IDMC review and recommendation. A total of 408 eligible subjects will be randomised in a 2:1 ratio to receive either XVR011 (272 subjects) or placebo (136 subjects).

Standard of care (SoC), according to local requirements will be allowed, except if listed in Table 6.5 Forbidden Concomitant Medications. Stratification will be done at randomisation for country and for fully vaccinated/prior SARS-CoV-2 infection. Subgroup analyses will include factors such as disease state, baseline serology, baseline viral load levels and duration of COVID-19 symptoms prior to study treatment.

For both Part 1 and Part 2 the study will consist of 3 periods: Screening (Day -1), Treatment period (Day 1), and Endpoint Assessment period (7 to 8 visits, Day 2 to Day 29); for Part 2 there will be an additional Follow-up period (2 visits, Day 60 and Day 90):

- **Screening (Day -1):** Subjects who are hospitalised and provide informed consent will undergo screening assessments as soon as possible after presentation with COVID-19 to evaluate their eligibility based on the inclusion and exclusion criteria. If eligible, the subject may be randomised (e.g for Part 1 this means IWRS treatment registration).
- **Treatment period (Day 1):** Within 12 hours of randomisation, a single intravenous infusion of study treatment will be started under medical supervision for the whole duration of the infusion and for two hours after the end of the infusion. This treatment will be administered in addition to SoC treatment.

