The IDMC will be asked to make a recommendation to progress to Part 2 (phase 2 design) of this study with the recommended dose based on the interim analysis of the Phase 1a study in 30 healthy subjects, supplemented with the available data from Part 1 of this study, even if not all Part 1 cohorts have reached the planned enrolment. This is due to recruitment challenges in Part 1 of this study resulting from low hospitalisation rate and reluctance of sites to participate and enrol patients in a phase I trial.

**Part 2 (Phase 2):** Part 2 consists of a double-blind, randomised, placebo-controlled Phase 2 study to evaluate the efficacy, safety, PK, and PD of XVR011 administered at the recommended dose level based on the IDMC review and recommendation. A total of 408 eligible subjects will be

randomised in a 2:1 ratio to receive either XVR011 (272 subjects) or placebo (136 subjects). Standard of care (SoC), according to local requirements will be allowed, except if listed in Table 6.5 Forbidden Concomitant Medications. Stratification will be done at randomisation for country and for fully vaccinated/prior SARS-CoV-2 infection. Subgroup analyses will include factors such as disease state, baseline serology, baseline viral load levels and duration of COVID-19 symptoms prior to study treatment.

For both Part 1 and Part 2 the study will consist of 3 periods: Screening (Day -1), Treatment period (Day 1), and Endpoint Assessment period (7 to 8 visits, Day 2 to Day 29); for Part 2 there will be an additional Follow-up period (2 visits, Day 60 and Day 90):

- **Screening (Day -1):** Subjects who are hospitalised and provide informed consent will undergo screening assessments as soon as possible after presentation with COVID-19 to evaluate their eligibility based on the inclusion and exclusion criteria. If eligible, the subject may be randomised (e.g for Part 1 this means IWRS treatment registration).
- **Treatment period (Day 1):** Within 12 hours of randomisation, a single intravenous infusion of study treatment will be started under medical supervision for the whole duration of the infusion and for two hours after the end of the infusion. This treatment will be administered in addition to SoC treatment.

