The proposed population is subjects, in whom the viral load is causing mild to moderate symptoms and who require supportive therapy such as hospitalised monitoring, treatment or supplemental oxygen but who are not in need of mechanical ventilation (i.e., level 4 or 5 of the 8-point ordinal scale). The aim of treatment with XVR011 is to neutralise the virus, to reduce the severity of the disease, and to prevent progression to severe complications such as ARDS or other major organ dysfunctions. Recovery is defined as reaching level 3 of the 8-point ordinal scale (i.e., subjects are hospitalised but no longer require supplemental oxygen or ongoing medical care for COVID-19) or less (subjects are no longer hospitalised for treatment of COVID-19). See also Section 2.1 and Section 2.2.

Study treatment will be administered in addition to SoC to limit the risk of disease progression for subjects randomised to placebo. For Part 2, concomitant use of remdesivir will be allowed as SoC, according to local guidelines.

Other small molecule antiviral agents such as molnupiravir and PF-07321332/ ritonavir may be continued at the discretion of the Investigator if they have been started prior to hospital admission for treatment of COVID-19 in accordance with their authorised use. However, they are not allowed if they are to be started once the subject is in hospital and in screening or already enrolled in the study.

Treatment with a SARS-CoV-2 neutralising monoclonal antibody for the current infection is not allowed with 4 weeks before and during the study, because of the similar mechanism of action and long half-life.

Stratification will be done at randomisation for country and for fully vaccinated/prior SARS-CoV-2 infection.

Subgroup analyses will include factors such as disease state, baseline serology, baseline viral load levels and duration of COVID-19 symptoms prior to study treatment.

Secondary endpoints to further evaluate efficacy include total duration of oxygen supplementation, proportion of subjects requiring mechanical ventilation or ICU transfer, subject-reported assessment of COVID-19-related symptoms following FDA Guidance for Industry (September 2020) and changes from baseline in viral load to evaluate antiviral activity.

Safety assessments will include standard adverse event reporting, physical examination, vital signs and ECGs, as well as the assessment of infusion related reactions (IRR) and hypersensitivity reaction.

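### Table 6–5 forbids all small-molecule anti-SARS-CoV-2 drugs in both study parts, while Section 4.2 allows remdesivir as standard of care in Part 2

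*Protocol*

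**What the plan says.** Table 6–5, in Section 6.5.1 of the protocol, has a row for "Small molecule anti-SARS-CoV-2 medical product" with the restriction "From signature of ICF up to EOS". Neither the table title, the row nor the footnote limits it to Part 1 or names an exception. The table just before it, Table 6–4, is headed "Restricted concomitant medications Part 1 only" and names remdesivir.

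Section 4.2 states: "For Part 2, concomitant use of remdesivir will be allowed as SoC, according to local guidelines". Its next paragraph reads: "Other small molecule antiviral agents such as molnupiravir and PF-07321332/ ritonavir may be continued at the discretion of the Investigator", on condition that they were begun before admission in line with their authorised use. It then adds that "they are not allowed if they are to be started once the subject is in hospital and in screening or already enrolled".

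The Synopsis (Overall Design) links standard of care in Part 2 to the table: "Standard of care (SoC), according to local requirements will be allowed, except if listed in Table 6.5 Forbidden Concomitant Medications". Section 4.1 repeats the rule.

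**The concern.** Two rules cover the same Part 2 subject over the same period and give opposite answers on remdesivir. Because the Synopsis and Section 4.1 make Table 6–5 the list of exceptions to standard of care, a permission granted as standard of care cannot override the table.

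Two things are at stake. The first is care: Section 4.2 explains that study treatment is added to standard of care to limit the risk of progression in the placebo arm, and a site applying the table literally would withhold or stop an antiviral that the design means to allow. The second is data handling: the same remdesivir use could be coded as a deviation at one site and as compliant at another. Those records feed the decision on who leaves the per-protocol set, which Section 9.3 uses to show robustness of the primary result.

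**Working it through.** The point is a comparison of rules, and the protocol states no figure to reproduce.

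**Is remdesivir in the class that Table 6–5 forbids?** Yes, on the protocol's own wording. In Section 4.2 the paragraph after the remdesivir permission opens with the word *other* before naming small-molecule antivirals, which puts remdesivir in that class. Table 6–4 and exclusion criterion 14 name it among products with possible or demonstrated anti-SARS-CoV-2 activity.

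**Does the row apply to Part 2?** Yes. Table 6–4 is limited to Part 1 in its title; Table 6–5 is not, and the Synopsis and Section 4.1 cite Table 6–5 in their description of Part 2.

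**The rules side by side for a Part 2 subject, after consent:**

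| Situation | Section 4.2 | Table 6–5 as written |
|---|---|---|
| Remdesivir as standard of care | Allowed | Forbidden |
| Molnupiravir or PF-07321332/ritonavir begun before admission, continued | Allowed at the Investigator's discretion | Forbidden after consent |
| Either of those agents newly started in hospital, in screening or after enrolment | Not allowed | Forbidden once consent is signed |

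The first two rows conflict. In the second, the table does not bar use before consent, but read literally a ban that starts at consent stops continued use. The third row agrees for any start after consent.

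**Which text is out of line?** Table 6–4 and exclusion 14 restrict remdesivir in Part 1 only. Both fit Section 4.2. The small-molecule row of Table 6–5 is the one that does not.

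**Extent.**
- Window in Part 2 (Synopsis, Treatment Groups and Duration): screening 1 + treatment 1 + endpoint assessment 28 + extended follow-up 61 = 91 days, ending at Day 90.
- Subjects covered by the row: 408 (272 XVR011, 136 placebo).
- Remdesivir use rate: not given. The number affected could lie anywhere from 0 to 408. For each assumed 10 percentage points of use, equal in both arms: 408 × 0.10 = 40.8, made up of 272 × 0.10 = 27.2 on XVR011 and 136 × 0.10 = 13.6 on placebo.
- Subjects lost from the full analysis set through a concomitant-medication deviation: 0 of 408, because Table 9–2 defines that set for Part 2 as all randomised subjects, analysed as randomised.
- Subjects lost from the per-protocol set: not determined. Table 9–2 excludes for deviations that affect the analyses, and Section 9.4.1 leaves the decision to a blinded review meeting.

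**The case against.** The strongest reply is that the intent is plain. Section 4.2 gives a specific Part 2 permission, and both Part 1 restrictions on remdesivir would be largely redundant during the study if Table 6–5 already barred it throughout. The row's start at consent also suggests that it was meant for new starts of the other agents. On this view it is a drafting omission. Section 6.5 sends questions on concomitant therapy to the Medical Monitor, and Section 6.5.1 says study treatment is added to local standard of care, so withheld care is a possibility and has not been shown. The blinded review can classify all remdesivir use by one rule whatever sites recorded. Use by all 408 subjects is also implausible: Section 6.5.1 describes an EU authorisation tied to pneumonia needing oxygen and a WHO recommendation against use, while subjects at level 4 of the scale, who need no oxygen, are eligible.

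Much of this stands as a limit on consequences. The upper end of the range is only a bound, harm to care is a risk and not a demonstrated effect, and no bias in the primary result follows. It does not remove the conflict. Intent shows which text to correct, but nothing in the protocol takes remdesivir out of the row, and two sections make that table decisive. Case-by-case queries do not replace a rule in a protocol that allows no waivers (Section 8) and requires exact adherence (Section 10.1.11).

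**Conclusion.** The concern holds. Table 6–5 forbids in Part 2 a drug that Section 4.2 allows and, read literally, also stops continued use of agents that Section 4.2 lets run on. This is a wrong rule in the table that sites will work from, and it should be fixed. It applies to all 408 Part 2 subjects over 91 days. How many would have an ambiguous deviation status depends on a use rate that the protocol does not give: about 41 per 10 percentage points of use (27 XVR011, 14 placebo), assuming equal use in both arms. The primary analysis population is unaffected, and exclusion from the per-protocol set is not automatic. The conclusion rests on the protocol text alone and on reading Section 4.2 as the sponsor's intent for Part 2, which Table 6–4 and exclusion 14 support.

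**What to change.** Amend the small-molecule row of Table 6–5 so that, for Part 2:

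- remdesivir given as standard of care under local guidelines is exempt;
- other small-molecule antivirals begun before hospital admission, in line with their authorised use, may continue at the Investigator's discretion;
- only new starts of those other agents in hospital, during screening or after enrolment, are forbidden.

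Leave Part 1 under Table 6–4. Notify sites, and have the blinded data review classify deviations and per-protocol exclusions against this single rule. If the sponsor does intend a complete ban, delete the Section 4.2 permissions instead.

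The cost is one amended table row and a site notification. Sample size, endpoint and primary analysis do not change.
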